## Hypothesis

There is no significant difference in the surgical outcome between the use of local anesthesia versus saddle block for open hemorrhoidectomy of uncomplicated 3rd- or 4th-degree hemorrhoids.

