## Methodology

### Study design

This study will be a prospective equivalence randomized, double-blind controlled trial conducted in the department of surgery at Kampala International University Teaching Hospital (KIU-TH), western Uganda.

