### Sample size determination

The randomized control trial assumes a null hypothesis that the mean postoperative pain scores after hemorrhoidectomy using local anesthesia are not different from that done under saddle block by a clinically relevant amount. Since the primary outcome measure was a continuous variable (i.e., pain level measured using a visual analog scale), the formula for an equivalence design in randomized control trials by Zhong et al. [15] was used.$$\boldsymbol{N}=\mathbf{2}\times {\left\{\frac{{\boldsymbol{Z}}_{\mathbf{1}-\propto}+{\boldsymbol{Z}}_{\mathbf{1}-\boldsymbol{\beta}}}{\boldsymbol{\delta}}\right\}}^{\mathbf{2}}\times {\boldsymbol{S}}^{\mathbf{2}}$$

where

***N***sample size per group

***Z***_***1−α***_standard normal deviate for a two-sided test used in equivalence trials (1.96 for 95% confidence interval)

***δ***clinically admissible margin of equivalence design as a difference

***α***type I error associated with rejecting the null hypothesis when it is true; (0.05) for 95% confidence interval

***β***type II error associated with the alternative hypothesis, assumed to be 0.20 for a statistical power of 80%

**(1−*****β*****)**the probability of rejecting the null hypothesis when it is false, i.e., *Z*_1−*β*_ = 0.845 for statistical power of 80%

***S***^**2**^pooled standard deviation of both comparison groups

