### Data processing and analysis plan

Data will be statistically analyzed using IBM Statistics SPSS for Windows 23.0. The primary outcome will analyze all randomized patients (on an intent-to-treat (ITT) basis) and per-protocol (PP) population. The mean pain scores at rest and their standard deviations will be computed and compared using one-way ANOVA tests. VAS will be stratified as ordinal (0 as no pain, 1–3 as mild, 4–6 as moderate, and 7–10 as severe); the significance of the difference in the mean scores between local and saddle groups will be determined by the Kruskall-Wallis (*H*) test at 95% confidence interval, regarding *p* < 0.05 as statistically significant; furthermore, the mean pain scores will be analyzed for significant differences in the area under the curve (AUC) for VAS (2-sample *t*-test). The mean operative time and standard deviation will be computed for each technique of open hemorrhoidectomy. Cross tabulation will be performed between the two open hemorrhoidectomy techniques for categorical cost-effective analysis. The difference in the means will be compared using the *t*-test and their corresponding two-tailed p-value, regarding *p* < 0.05 as statistically significant.

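### The trial is planned as an equivalence trial with a margin, but its analysis contains only tests of difference at p < 0.05, which invites reading non-significance as equivalence

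*Protocol article*

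**What the plan says.** The Study design section states: "This study will be a prospective equivalence randomized, double-blind controlled trial". Sample size determination uses a formula for equivalence designs and defines δ as the "clinically admissible margin of equivalence design as a difference". The value entered for δ is 0.73, the difference in mean pain scores seen in an earlier trial.

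The same section sets as its null that mean pain scores under local anesthesia "are not different from that done under saddle block by a clinically relevant amount". The Hypothesis section reads: "There is no significant difference in the surgical outcome between the use of local anesthesia versus saddle block for open hemorrhoidectomy".

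Data processing and analysis plan then names the tests:
- one-way ANOVA on mean pain scores;
- for VAS grouped into four ordered categories, "the significance of the difference in the mean scores between local and saddle groups will be determined by the Kruskall-Wallis" test;
- for the AUC, "the mean pain scores will be analyzed for significant differences in the area under the curve (AUC) for VAS", by a two-sample t-test.

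The criterion throughout is p < 0.05. That section mentions a 95% confidence interval only as a significance level. Neither the margin nor a comparison of an interval with a margin appears there.

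**The concern.** In an equivalence trial the null is that the arms differ by at least the margin, and the data must reject it. Here the position to be supported serves as the null, and the tests can only reject it in favour of a difference. A non-significant result from such a test does not show that the arms are alike: a small or noisy trial produces one easily.

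The error that matters is concluding equivalence when the arms differ by the margin or more. Nothing in the analysis section controls it. The article intends the result to inform policy (Study rationale) and presents it as level 1 evidence (Study strengths), so a wrong equivalence conclusion would have consequences.

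**Working it through.** **Inputs**, all from Sample size determination unless noted:
- δ = 0.73 VAS points;
- S = 1.9, described as the average of arm SDs 2.356 and 1.479;
- z values 1.96 and 0.845;
- 104 per group from the formula, 26 after adjustment, 29 after allowing for 10% loss;
- two-tailed p < 0.05 (Data processing and analysis plan).

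**1. The plan's own figure.** N = 2 × ((1.96 + 0.845)/0.73)² × 1.9² = 2 × 14.76 × 3.61 = 106.6, so 107 against the stated 104 (within 3%). This confirms that 0.73 was used as the margin. Also 26/0.9 = 28.9, so 29.

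**2. How often the planned kind of test is non-significant when the true difference equals 0.73.** For a two-sample t-test on mean VAS, SE = S × √(2/n), noncentrality = 0.73/SE and df = 2n − 2. P(p ≥ 0.05) is 1 minus the power from the noncentral t.
- n = 29, S = 1.9: SE 0.499, noncentrality 1.463, df 56, critical t 2.003: **69.9%**.
- n = 26, S = 1.9: SE 0.527, noncentrality 1.385, df 50: **72.6%**.
- n = 29, S = 1.479: SE 0.388, noncentrality 1.879: **54%**.
- n = 29, S = 2.356: SE 0.619, noncentrality 1.180: **79%**.

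At n = 29 and S = 1.9, the figure is 50% for a true difference of 1.0 point and 16% for 1.5 points. At 104 per arm and S = 1.9, the figure at 0.73 would be about 21%. A margin-based test caps the error at the margin at 2.5% (whole 95% CI inside) or 5% (whole 90% CI inside), whatever the sample size.

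**3. What a margin-based test could deliver at 29 per arm.** Half-width = t × SE.
- S = 1.9, 95% CI: 2.003 × 0.499 = 1.00. 90% CI: 1.673 × 0.499 = 0.83. Both exceed 0.73. With identical arms, the chance of showing equivalence is below 0.01% (95%) or about 0.5% (90%).
- S = 1.479, the most favourable SD given: half-widths 0.78 and 0.65, chance about 2.4% and 17%.

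**4. Size needed for 80% power with identical arms and S = 1.9** (normal approximation, before loss).
- 95% CI: 2 × ((1.960 + 1.282) × 1.9/0.73)² ≈ 142.4, so about 143 per arm.
- 90% CI: 2 × ((1.645 + 1.282) × 1.9/0.73)² ≈ 116.0, so about 117 per arm.

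**The case against.** A reader might infer that the trial will declare equivalence whenever p ≥ 0.05, with a false-equivalence rate of about 70%. The article does not say that. The Interim analysis section even contemplates stopping if a treatment difference looks unattainable, which is the language of a trial seeking a difference. So the 70% is a false-equivalence rate only under an inferred decision rule. The inference is reasonable, because the hypothesis is no significant difference and p < 0.05 is the only rule given. If it is wrong, the article has no rule for concluding equivalence at all.

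The 70% also does not describe the named primary variable. That variable is the AUC of VAS (Primary outcome variable), for which no SD or margin is given, and the rank test runs on four categories. The 0.73 is an earlier trial's observed difference, not a clinically argued margin. These limits stand, so the figure is an illustration with a range.

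The null in the sample-size section is not a bare statement of no difference, since it is qualified by clinical relevance. It is still reversed: it makes the equivalence claim the null.

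A reader might also infer three competing primary tests. That goes too far. The AUC is named as the primary measure and is assigned the t-test, and with two arms one-way ANOVA is the same test as an equal-variance t-test. Ranking supportive tests can be left to an analysis plan.

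A separate analysis plan might exist, but the article itself fixes the tests and the criterion, and these contradict its design.

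**Conclusion.** The concern holds in this form: the design and sample size are for equivalence, the hypotheses are reversed, and the analysis contains only difference tests that never use the margin. This is a contradiction within the text, not missing detail.

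Its size can only be illustrated. Under a t-test on mean VAS with SD 1.9 and 0.73 as the margin, non-significance at the margin is about 70% at 29 per arm and 73% at 26 evaluable, with 54% to 79% at 29 per arm over SDs 1.479 to 2.356. The rates for the AUC and the rank test cannot be computed from the article. Whether non-significance would in fact be reported as equivalence is not stated.

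**What to change.** - Restate the null as |difference| ≥ margin and the alternative as |difference| < margin, in both the Hypothesis and Sample size determination sections.
- Make the primary analysis the between-arm difference in one pain summary, with a two-sided 95% CI, as the sample-size section's 1.96 implies. Its scale must be one for which the margin is defined: mean VAS, or AUC divided by time so that it is in VAS points.
- Claim equivalence only if the whole CI lies within ± the margin in both the ITT and per-protocol sets. Otherwise report that equivalence was not shown.
- Make the ANOVA and the categorised rank test supportive. Adjustment for hemorrhoid degree is optional.

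The edits are to wording, and the interval comes from the same software. The real cost is that, at 29 per arm and SD 1.9, equivalence within 0.73 almost certainly cannot be shown, even with identical arms. The result should therefore be presented as an estimate with its CI. An interim look at the outcomes took place on 10 March 2022, and 45 of 58 patients were registered by 7 April 2022. The change, including any choice of margin, should be dated, justified and reported as made after the interim analysis.

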### Study variables

#### Primary outcome variable

The occurrence of pain following open hemorrhoidectomy will be determined in both groups using the area under the curve (AUC) for visual analog scale (VAS). The VAS will be used in an interval of 2, 4, and 6 h and 7 days postoperatively (the lower end of the scale labeled “0” means no pain while the upper end of the scale “10” signifies the worst imaginable pain).

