#### Independent variables

Data will be captured on preoperative independent variables such as gender, age, ASA level, and degrees of the hemorrhoids.

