### Randomization and blinding

After fulfilling the enrollment criteria and obtaining the informed consent, the participants will be allocated randomly by assistant researchers well trained to either the local anesthesia group (group A) or the saddle block group (group B) by using envelope allocation concealment whereby half of the envelopes will contain a chit with letter A while the other half will have a chit with letter B signifying local anesthesia and saddle block, respectively. The content of the envelope will be opened once the patient is in the theater, and the patients and outcome assessors will be blinded about the anesthesia.

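### The pain comparison is unadjusted although degree of hemorrhoids and age are recorded before surgery: valid, but it forgoes a small, nearly free gain in precision and protection against chance imbalance

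*Protocol article*

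**What the plan says.** All references are to the protocol article.

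- **Primary outcome variable:** pain "will be determined in both groups using the area under the curve (AUC) for visual analog scale (VAS"), from scores at 2, 4 and 6 hours and at 7 days.
- **Data processing and analysis plan:** three pain comparisons are named. First, "The mean pain scores at rest and their standard deviations will be computed and compared using one-way ANOVA tests". Second, VAS in ordered categories is compared by a Kruskal-Wallis test. Third, "the mean pain scores will be analyzed for significant differences in the area under the curve (AUC) for VAS (2-sample *t*-test"). None carries a covariate.
- **Independent variables:** "Data will be captured on preoperative independent variables such as gender, age, ASA level, and degrees of the hemorrhoids". No baseline pain score is listed. The analysis plan gives these variables no part in the outcome comparison.
- **Missing data:** clinical characteristics are used to compare patients lost to follow-up and crossovers with those retained.
- **Randomization and blinding:** "half of the envelopes will contain a chit with letter A while the other half will have a chit with letter B". No stratification factor is described.
- **Sample size determination:** 29 per arm, with a difference of 0.73 and an SD of 1.9.

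**The concern.** Severity of disease could plausibly affect pain after surgery. With 29 patients per arm and no stratification described, 3rd- and 4th-degree disease can fall unevenly between the arms, and the named tests do not correct for it. Any variance in pain that degree and age explain stays in the error term and widens the interval for the arm difference. A chance imbalance in severity can also create an apparent difference or mask a real one. Masking matters in a trial that calls itself an equivalence trial.

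This is a point about a stated choice. The analysis plan names unadjusted tests, including the one on the primary outcome, so a later document that adjusted would depart from this text.

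**Working it through.** **Inputs from the article:** S = 1.9, difference or margin 0.73, 29 per arm (58 in total), two-sided 5%: "standard normal deviate for a two-sided test used in equivalence trials (1.96 for 95% confidence interval"). Power: "assumed to be 0.20 for a statistical power of 80"%.

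**Inputs not in the article, so assumed:** R² (the share of pain variance explained by the covariates), the prevalence of 4th-degree disease, and its effect on pain.

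**1. The plan's own figures.** N = 2 × ((1.96 + 0.845)/0.73)² × 1.9² = 106.6, so 107 per group against the stated 104 (within 3%). A finite-population correction on 33 cases gives 104/(1 + 103/33) = 25.2, so 26. Allowing 10% loss, 26/0.9 = 28.9, so 29.

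**2. Unadjusted test, 29 per arm.** SE = 1.9 × √(2/29) = 0.499. The 95% CI half-width is 2.003 × 0.499 = 1.00 (56 df). Noncentral-t power at a difference of 0.73 is 30.1%.

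**3. Adjusted for p covariates.** Variance relative to the unadjusted test = (1 − R²) × (1 + p/(58 − p − 3)). For p = 2 the second factor is 1 + 2/53 = 1.038, with 54 df.

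| R² (assumed), p = 2 | Relative variance | 95% CI half-width | Power at 0.73 |
|---|---|---|---|
| Unadjusted | 1.00 | 1.00 | 30% |
| 0 | 1.04 | 1.02 | 29% |
| 0.07 | 0.97 | 0.98 | 31% |
| 0.15 | 0.88 | 0.94 | 33% |
| 0.25 | 0.78 | 0.88 | 37% |

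Break-even R² = p/(58 − 3): 1/55 = 0.02 for one covariate, 2/55 = 0.04 for two, 4/55 = 0.07 for all four. At R² 0.25, using all four gives 36% power against 37% with two.

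**4. What a plausible severity effect implies.** Suppose 4th degree adds 1 VAS point and half the patients have it (both assumptions). The variance due to degree is 0.5 × 0.5 × 1² = 0.25, so R² = 0.25/1.9² = 0.25/3.61 = 0.07. That is the 31% row. For degree alone to reach R² 0.25 it would have to add 1.9 points, since 0.25 × 1.9² = 0.9025 and 0.9025/3.61 = 0.25.

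**5. Chance imbalance.** A gap of 20 percentage points means 6 or more patients (6/29 = 20.7%).
- Exactly 29 of 58 with 4th degree (hypergeometric): 0.114. The gap in counts must then be odd, so it has to reach 7.
- 28 or 30 of 58: 0.189.
- Each patient independently at 50%: 0.148.

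The range is therefore about 11% to 19%. With a 1-point effect, a 20-point gap shifts the arm difference by 0.2 × 1 = 0.2, which is 0.2/0.73 = 27% of the margin and 0.2/0.499 = 0.4 standard errors.

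**6. Equivalence.** For a 95% interval to fit inside ±0.73 its half-width must be below 0.73. That needs R² of about 0.48 with one covariate and 0.49 with two.

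**The case against.** The strongest reply is that nothing here is wrong. A two-sample t-test is valid under randomization, chance imbalance does not bias it, and its standard error already allows for such imbalance. Recording baseline characteristics without modeling them is ordinary, and the article promises no adjusted model. Covariate lists often sit in an analysis plan or full protocol, neither of which is shown. The gain is assumed, could be slightly negative, and no baseline pain score is available as a stronger covariate.

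Most of this stands. The validity of the t-test is conceded, and so is the dependence on an unknown R². The argument about an unseen document has less force, because the article names the unadjusted tests outright.

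A reader might infer three stronger points that the article does not support:

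- **That the unadjusted analysis is biased or contradicts the list of independent variables.** It does neither.
- **That adjustment lifts power from 30% to 38%.** That figure needs R² 0.25 with a single covariate. Degree and age together give 37% at that R², and a 1-point severity effect implies about 31%.
- **That adjustment would rescue the equivalence claim.** The half-width stays above 0.73 until R² is near 0.48 to 0.49. The cut from 104 to 26 per group is a far larger loss.

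**Conclusion.** The point holds as a modest improvement in method. The named pain tests ignore two recorded variables that could predict pain, in a small trial with no stratification described. Using them would cost about 1 point of power if they are unrelated to pain. It would gain about 1 point at R² 0.07, 3 at 0.15 and 7 at 0.25, with the half-width falling from 1.00 to 0.98, 0.94 and 0.88. It would also correct the estimate for a severity gap of 20 points or more, which arises in roughly 11% to 19% of allocations if prevalence is near 50%.

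The result rests on the assumed R², prevalence and severity effect. The 0.73 and 1.9 are mean-VAS figures, so the absolute numbers only illustrate the AUC; the relative variances do not depend on the scale. The power figures are for detecting a difference of 0.73 and are not the chance of showing equivalence, which adjustment does not bring within reach at 29 per arm.

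**What to change.** In the data processing and analysis plan, make the main pain analysis a linear model on VAS AUC with arm as the factor and degree (3rd or 4th) and age as prespecified covariates. Report the adjusted arm difference with its 95% CI. Keep the two-sample t-test as a sensitivity analysis. Stop at two covariates, because with 58 patients all four raise the break-even R² from about 0.04 to 0.07.

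Fix the covariates before the arms are compared again. The article reports an interim analysis on 10 March 2022, with outcomes to be evaluated by arm, so a later choice could appear to be guided by results. Adjustment remains possible now, whereas stratification could not reach the 45 patients already registered by 7 April 2022.

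The cost is a sentence or two of text and two degrees of freedom. The variables are already collected and the named software fits the model.

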#### Secondary outcome variable

The mean operative time from anesthesia induction to the end of open hemorrhoidectomy will be recorded in both groups.

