#### Tertiary outcome variable

The tertiary outcome is the cost-effectiveness of the 2 surgical approaches in relation to the amount of materials used in the 2 arms.

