### Ancillary and post-trial care

The outcome of the study may indirectly help participants to obtain care during study time and will be recognized during publications. Diverse outcomes, e.g., too much pain, will result in converting from local to SA (crossover) and getting other analgesics other than those prescribed in the trial.

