### Trial discontinuation

The trial will be discontinued for individual patients due to non-adherence, e.g., not completing the specified duration of follow-up, diverse outcomes, e.g., too much pain resulting in converting from local to GA (cross over) and getting other analgesics other than those prescribed in the trial.

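### Rules that remove failed or converted patients after allocation leave the operative-time and cost comparisons without an all-randomized analysis to protect them

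*Protocol article*

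**What the plan says.** The Data processing and analysis plan states: "The primary outcome will analyze all randomized patients (on an intent-to-treat (ITT) basis) and per-protocol (PP) population". For operative time it then says "The mean operative time and standard deviation will be computed for each technique of open hemorrhoidectomy", and for cost "Cross tabulation will be performed between the two open hemorrhoidectomy techniques for categorical cost-effective analysis". Neither of these two sentences names a population.

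The outcome definitions are worded by allocation. Secondary outcome variable: "The mean operative time from anesthesia induction to the end of open hemorrhoidectomy will be recorded in both groups". Tertiary outcome variable: "cost-effectiveness of the 2 surgical approaches in relation to the amount of materials used in the 2 arms".

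Several other sections deal with patients whose anesthetic does not work:

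- **Exclusion criteria** list a failed anesthetic technique.
- **Interim analysis** and **Unblinding** leave it to the principal investigator to withdraw a patient for failure of the technique or loss to follow-up.
- **Ancillary and post-trial care** says that too much pain "will result in converting from local to SA (crossover".
- **Trial discontinuation** gives as a reason for stopping an individual patient "too much pain resulting in converting from local to GA (cross over".
- **Missing data** compares crossovers and patients lost to follow-up with those retained.

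Randomization and blinding says that the envelope is opened when the patient is already in theater.

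**The concern.** A technique cannot fail, and a patient cannot convert, before the envelope is opened and the anesthetic given. The exclusion, withdrawal and discontinuation rules therefore act after randomization, on an event that depends on the allocated treatment. For pain, the intention-to-treat sentence at least opposes such removal, though the two conflict. For operative time and cost nothing in the document opposes it.

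A failed or converted case is likely to be long and to use the materials of two anesthetics. These are the cases that a comparison of starting with one technique against starting with the other has to include. The withdrawal decision also rests with the principal investigator, who injects the local anesthetic and performs every operation, and so knows the arm.

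Operative time and cost-effectiveness are specific objectives ii and iii, and the Introduction rests much of its case for local anesthesia on them.

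**Working it through.** **Step 1. What each outcome is protected by.**

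| Outcome | Population named | Rules that can remove failures |
|---|---|---|
| Pain | All randomized, and per-protocol | Yes, in conflict with all-randomized |
| Operative time | None | Yes, unopposed |
| Cost | None | Yes, unopposed |

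**Step 2. Which arms the rules reach.** The failed-technique exclusion and the withdrawal rule name no arm, so they cover failed saddle blocks too; the Introduction itself lists failed block among saddle-block problems. Conversion is described only from local anesthesia.

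**Step 3. Inputs.** The protocol gives 29 patients per arm (26 raised for 10% loss; 26 / 0.90 = 28.9). It gives no planning value for operative time or cost, and no failure or conversion rate, so there is no stated figure to reproduce. I assume:

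- equal mean times in the two arms when nothing fails;
- X = 15 to 30 extra minutes for each failed case;
- kL local failures and kS saddle-block failures.

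**Step 4. Formula.** With all randomized patients kept, the local-minus-saddle difference is (kL − kS) × X / 29. With failures dropped from both arms it is 0. The shift caused by dropping is therefore

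shift = −(kL − kS) × X / 29,

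where a negative value favors local anesthesia.

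**Step 5. Results.**

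| kL / kS | X = 15 min | X = 30 min |
|---|---|---|
| 3 / 0 | −45/29 = −1.6 | −90/29 = −3.1 |
| 6 / 0 | −90/29 = −3.1 | −180/29 = −6.2 |
| 3 / 3 | 0.0 | 0.0 |
| 1 / 3 | +30/29 = +1.0 | +60/29 = +2.1 |
| 0 / 3 | +45/29 = +1.6 | +90/29 = +3.1 |

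The sign follows the difference in failure counts, or in minutes per failure if X differs between arms. The same algebra holds for cost, with extra materials in place of extra minutes.

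**The case against.** **Silence is not restriction.** Naming populations for secondary outcomes is often left to a full protocol or statistical analysis plan, and neither is shown. This would settle the matter if the article only left the population open. But it also states rules that take failed and converted patients out after allocation, and those rules are what produce the biased comparison. A fuller plan may resolve this; the text shown does not.

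**The wording about techniques.** A reader might infer that time and cost will be analyzed by anesthesia received. The document does not support that. The two outcome definitions speak of groups and arms, and the Discussion part of the Abstract and the Interim analysis section use technique as an ordinary word for an arm. The removal comes from the other sections, not from this sentence.

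**The direction.** A reader might also infer that both comparisons necessarily tilt toward local anesthesia. That does not follow, because failed saddle blocks can be removed as well and the table above shows the shift vanishing or reversing.

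**Reclassification.** Nothing says that converted cases are counted under saddle block. One section has them converted to general anesthesia, which could not be counted there.

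**Large false-positive rates.** Suitable assumptions give striking figures: 20% of the local arm failing at 40 extra minutes, an SD of 10 to 15 minutes and no saddle failures give rejection rates of 51 to 85% at a nominal 5% (47 to 80% allowing for the smaller local arm). The milder case of 5% failing at 20 extra minutes gives 6 to 7%. Every input beyond the arm size and the 5% level is assumed, so these figures describe the assumptions rather than this trial.

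**Conclusion.** The point holds in a limited form. The protocol sets rules that can remove technique failures and conversions after allocation, and states an all-randomized analysis only for pain. Operative time and cost can therefore be compared in groups that are no longer the randomized ones. A bias favoring local anesthesia is plausible because conversion is described only from that arm, but the documents establish neither its direction nor its size. Under the assumed 3 failures against 0 it is about 1.6 to 3.1 minutes.

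The root of the problem is the conflict between the removal rules and analysis by allocation, which touches the primary pain analysis too. It should be corrected, since two of the three specific objectives depend on it.

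**What to change.** 1. In the Data processing and analysis plan, state that operative time and cost are analyzed in all randomized patients by allocated group, with per-protocol as supportive, and refer to randomized groups rather than techniques.
2. For a failed or converted case, count time from the start of the first anesthetic to the end of surgery, and charge the materials of both anesthetics to the allocated arm.
3. Reconcile Exclusion criteria, Interim analysis, Ancillary and post-trial care, Trial discontinuation, Unblinding and Missing data with the intention-to-treat statement, so that technique failure or conversion does not remove a randomized patient's data from any outcome, pain included. The sections that name different anesthetics after conversion should also be made to agree; which is right is for the investigators.

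The cost is a few sentences in the analysis plan and matching edits in those sections, with no extra patients. Operative time and materials are known by the end of surgery, so later loss to follow-up need not remove them. The explicit time zero in the procedure section is tied to cleaning the back, so the start point for the local arm should be written down as well. The downside is a somewhat larger SD and possibly a less favorable figure for local anesthesia. Because an interim analysis of all outcomes has already taken place, the change should be dated and recorded as made after it.
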